**Methods:**

Five public hospitals in the Spanish National Health System, with diverse profiles, including one university hospital and four second-level hospitals, will be included. In total, 20 hospitalization wards will be randomized for this study by ward to one of two groups. Those in the first group receive an intervention that lasts 12 months implementing evidence-based practice in healthcare related to peripheral catheters through a multimodal strategy, which will contain updated and poster protocols insertion, maintenance and removal of peripheral venous catheters, technologies applied to e-learning, feedback on the results, user and family information related to peripheral catheter, and facilitation of the best evidence by face-to-face training session. Primary outcome measures: Incidence of adverse events associated with the use of peripheral venous catheters is measured by assessing hospital records. Secondary outcome measures: Nurses’ adherence to clinical practice guidelines, clinical outcomes, and the cost of implementing the multimodal intervention.

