### Secondary outcome measures: process evaluation

Nurses’ adherence to CPGs will be measured at 3, 6, 9, and 12 months with the following subcategories:1.1Multimodal intervention content will be delivered as planned (yes/no), and dosage will be delivered as often and long as planned (yes/no); face-to-face training session will be assessed by measuring the number of nurses who completed the Masterclass at the intervention phase. Feedback will be evaluated by checking the distribution of clinical audit results within intervention wards. Patient information will be assessed by monitoring the presence of informative leaflets on the ward (yes/no) and asking if the patient is aware of use of PVC and prevention recommendations for personal care. Facilitation will be measured by number of internal facilitators who completed the intervention.Clinical audits on use of PVC. Device utilization ratios will be measured by percentage of PVCs per hospital wards and number of PVC per patient. Documentation of PVC in nursing records will be assessed by percentage of fully completed records. PVC maintenance will be monitored by random, monthly clinical audits, which will document PVC size (16/18/20/22/24 gauge), site (dorsum of hand/forearm/antecubital region/upper arm), dressing integrity (clean/dry/intact), securement and time in situ (less 48 h/ between 48 and 96 h/more 96 h). Catheter tip will be measured by number of catheter tip extraction following removal of PVCs.Routine practice. Clinical effectiveness questionnaire for the prevention of PVC complications will be completed pre and post intervention. The questionnaire is made up of 35 questions in four sections, relating to general asepsis and skin antisepsis; PVC insertion, maintenance, and removal; PVC documentation; and patient and professional education.Clinical outcomes will be assessed using rates of unnecessary PVCs, rates of CRBSI, extravasation, obstruction and phlebitis, defined as per standard guidelines, and mean HLOS associated to PVC-BSIs at 3, 6, 9, and 12 months.The direct costs of implementing the multimodal intervention will be assessed using HLOS for patients and decrease rates of adverse events at 12 months (post intervention).EBCP environment:EBCP context: The contextual factors on the utilization of knowledge in clinical practice decisions and impact on hospital ward processes and practice will be assessed using the NWI tool pre-intervention. The variables are summarized into five main groups: nurses’ participation in hospital affairs; quality of nursing care; nurse management’s capacity, leadership, and support for nursing staff; size of the nursing workforce and adaptation of available human resources, and professional relation between doctors and nurses.EBCP individual: The opinions, attitudes, abilities and motivations of nurses and their links with the development of a culture of clinical practice based on the transfer of new knowledge to the healthcare given to patients will be assessed using EBPQ pre-intervention. The questionnaire is made up of 24 questions relating to professionals’ knowledge, use and attitudes towards EBCP.

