### Control group

The control ward will not receive the multimodal intervention and will continue with routine practice.

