### Intervention group

The intervention will last 12 months and will be based on a theoretical model on effective knowledge mobilization, integrating a multimodal strategy related to peripheral catheters clinical practice improvement which includes the following (Fig. 1): (1) implementation of recommendations trough up-to-date protocols and posters related to hand hygiene and aseptic measures, insertion, maintenance and removal of PVC [34]; (2) use of e-learning technologies [35–37]; (3) feedback on the results and messages addressed to healthcare professionals to facilitate adherence to recommendations [38]; (4) face-to-face training sessions [39]. Masterclass related to PVC insertion, maintenance, and removal will consist of information shared about recommendation of CPGs adapted according to the needs detected by means of the questionnaire on the effectiveness of the healthcare practice; (5) leaflets with information for patients and family/careers about peripheral catheters, in appropriate language [40]; and (6) support by internal facilitators, which will be key members of staff in the organizations, to adopt best evidence based on the PARIHS theoretical model [26, 41, 42].

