### Definitions

CRSBI: The following case definitions will be used to determine a diagnosis of CRBSI (see Fig. 1):
▪CRBSI type 1: Local PVC-related infection (no positive blood culture): Positive quantitative culture (103 CFU/ml) or semi-quantitative culture with more than 15 CFU from the tip of PVC and local signs of infection at the insertion site or in catheter lumen.▪CRBSI type 2: General PVC-related infection (no positive blood culture positive): positive quantitative culture (103 CFU/ml) or semi-quantitative culture with more than 15 CFU from the tip of PVC and that clinical signs improve within 48 h of catheter removal.▪CRBSI type 3: PVC-BSI associated with microbiologically confirmed with blood culture occurring 48 h before or after catheter removal and positive quantitative culture (103 CFU/ml) or a semi-quantitative culture with more than 15 CFU from the tip of PVC for the same microorganism.
(b)Phlebitis: An inflammation of the wall of a vein. If a blood clot in the vein causes the inflammation, then the condition is termed thrombophlebitis. This problem is characterized by persistent pain referred to PVC (2 h since the last administration), erythema, swelling, and palpable thrombosis of the cannulated vein.(c)Extravasation: Inadvertent leakage of a vesicant solution into surrounding tissue.(d)Obstruction: Following occlusion of the PVC, which can be partial (i.e., blood cannot be aspirated, but PVC can be flushed) or complete, whereby neither aspiration nor infusion are possible.

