### Blinding

Hypothesis and variables will be blind to prevent any selection bias that might arise in the nurses participating in the data collection process. All research assistants will be blinded to group allocation. Success of blinding will be assessed at study end using the James Blinding Index. Although FIREs and intervention wards will not be blinded, control wards will be blinded. Patients will be unaware of the intervention. [name] and [name] analyze the data, all will be blinded to group allocation.

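### The protocol says patients will be unaware of the intervention, yet one component is information given to patients on intervention wards only, so patient blinding to the intervention cannot be claimed

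*Protocol article*

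**What the plan says.** The Blinding section lists who is kept blind. On staff it says: "Although FIREs and intervention wards will not be blinded, control wards will be blinded". On patients it says, without qualification: "Patients will be unaware of the intervention".

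Other sections describe a component aimed at patients:

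- Abstract, Methods: the strategy includes "user and family information related to peripheral catheter".
- Intervention group, component 5 of 6: "leaflets with information for patients and family/careers about peripheral catheters, in appropriate language".
- Secondary outcome measures: process evaluation. Patient information is assessed by whether leaflets are present on the ward (yes/no), and by "asking if the patient is aware of use of PVC and prevention recommendations for personal care".
- Control group: "The control ward will not receive the multimodal intervention and will continue with routine practice".

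Phlebitis is part of the primary composite (Primary hypothesis). The Definitions section lists "persistent pain referred to PVC" among its features, with erythema, swelling and palpable thrombosis. The incidence is taken from hospital records (Primary outcome measures).

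**The concern.** One section denies patient awareness, while another treats it as evidence that the intervention was delivered. If component 5 works as intended, patients on intervention wards know more about catheter problems than those on control wards, and they know it because of the intervention.

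Two things are at stake. First, the trial report could claim a blinding property that the design does not have. Second, part of the primary outcome may depend on what patients tell staff. Pain is normally learned from the patient, although the protocol does not say how it is ascertained. Information given in one arm only could change how often, or how early, pain is mentioned and charted. Blinding the research assistants does not remove a difference that arose before the record was made.

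**Working it through.** **Step 1. The statements side by side.**

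| Question | Where | Answer in the protocol |
|---|---|---|
| Do patients know of the intervention? | Blinding | No |
| Is any component addressed to patients? | Abstract; Intervention group | Yes, leaflets and information |
| Do control wards receive it? | Control group | No |
| Is patient knowledge a delivery measure? | Process evaluation | Yes, for PVC use and prevention |

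The first answer is compatible with the others only if the intervention there means the trial, its hypothesis or the allocation. The sentence does not say so.

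Patients are asked about the subject of the leaflets, not about the leaflets themselves, and only the leaflets' presence on the ward is monitored. The protocol does not say whether control patients are asked too. The contradiction rests on the leaflets being part of the intervention. The question put to patients supports it but is not needed for it.

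**Step 2. Weight of phlebitis in the composite.** Inputs are the pilot rates in the Sample size section.

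- Sum of components: 16 + 6.8 + 18.1 + 3.2 = 44.1, which reproduces the stated global rate.
- Phlebitis share: 16 / 44.1 = 0.363, or 36%.

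**Step 3. Role of pain in the definition.** The four features are joined by *and*.

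- If all four are required, an extra report of pain adds a case only where the other three signs are already present.
- If any one suffices, an extra report of pain can make a case by itself.

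The protocol does not say which applies.

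**Step 4. Illustration only.** Assumptions: the 15% reduction is relative and applies equally to all components, components add as in the pilot, and recorded phlebitis on intervention wards changes by a fraction *k* through reporting alone. The relative reading fits the stated size: 44.1% against 37.5% with two-sided alpha 0.05 and power 0.80 needs 866 per arm, 1732 in total, and 1732 / 0.9 = 1925, close to the stated 1920.

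- Intervention composite = 44.1 × 0.85 + 16 × 0.85 × *k* = 37.485 + 13.6 × *k*.
- Apparent difference = 44.1 − that value.

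| *k* (assumed) | Intervention composite | Apparent difference |
|---|---|---|
| −20% | 34.8% | 9.3 points |
| −10% | 36.1% | 8.0 points |
| 0 | 37.5% | 6.6 points |
| +10% | 38.8% | 5.3 points |
| +20% | 40.2% | 3.9 points |

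Each 10% change in recorded phlebitis moves the composite by about 1.4 points against a planned 6.6. No figure in the protocol supports any particular *k*, and zero is as admissible as the rest.

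**The case against.** The strongest reply is that the sentence is loose rather than false. In a ward-randomised trial a patient can be handed a general catheter leaflet without learning that there is a trial, a hypothesis or an allocation. The rest of the Blinding section is about hypothesis and group allocation, and nothing says that the leaflet discloses them. This stands as a plausible account of what was meant. It does not rescue the wording, which denies awareness of the intervention itself.

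A reader might go further and infer that phlebitis will be over-recorded on intervention wards, hiding a true benefit and costing power. The document does not support that. The outcome comes from hospital records, the definition can be read as requiring all four features, and any reporting effect could run either way. Earlier reporting by informed patients might also prevent events, which would be a treatment effect and not bias.

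It is also fair to say that the unblinded staff on intervention wards, whom the protocol discloses, are probably a larger source of differential ascertainment. Correcting the patient sentence leaves that untouched. Some loss of patient blinding is hard to avoid when education is part of the intervention. None of this answers the contradiction, but it limits the weight of the consequence.

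**Conclusion.** The contradiction is internal and certain. As designed, patients on intervention wards are not blinded to the intervention. The most the trial could claim is that they are not told the hypothesis or the allocation, and the protocol does not currently say that.

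The consequence for the primary outcome is possible but undetermined. The exposed component is 36% of expected events on the pilot rates. The link to pain assumes that pain reaches the record through the patient's report, and its effect depends on whether pain alone makes a case. The table above shows how far the result could move under assumed changes in either direction. It does not estimate a bias, and no loss of power should be attributed to this point.

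**What to change.** Replace the sentence in the Blinding section with, for example: *Patients on intervention wards receive an information component and are not blinded to it; they are not told the study hypothesis or their ward's allocation.* Keep the second clause only if it is true. Reconcile the new text with the process evaluation and Intervention group sections.

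Report two sensitivity analyses of the primary composite, labelled as supportive:

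1. The composite without phlebitis.
2. Where signs are recorded separately, the composite counting phlebitis only when a sign other than pain is present.

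Neither removes bias from records likely made by unblinded ward staff, and the report should say so. If all four features are required for a case, the second analysis will equal the main one.

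The cost is one sentence and two analyses. The first analysis keeps 44.1 − 16 = 28.1 points, or 28.1 / 44.1 = 64% of expected events. With the same 15% relative reduction its expected difference is 28.1 × 0.15 = 4.2 points instead of 6.6, so it will be less precise and should not be read as a test in its own right. The second needs no new data if the signs are already charted separately, which the article does not show.

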## Discussion

Clinical implementation is a complex, multifaceted phenomenon [26] which requires a deep understanding of decision-making, knowledge mobilization, and sense-making in routine clinical practice [49]. Likewise, the inclusion of strategies that promote fidelity [50] to recommendations through multicomponent and multimodal interventions [51, 52] must be encouraged. The identification of barriers and constraints at the level of institutions and individuals involved should be the first step [53]. The use of a transfer model could counterbalance one of the greatest challenges for organizations, the evaluation of the impact of the implementation of research evidence in the professional context through quality indicators associated with prevention and control of infections [54, 55]. Although life-threatening adverse events such as CRBSIs have a low incidence in our setting, the volume of PVC use amplifies its importance in terms of morbidity, mortality, and patient safety. An important limitation may be the low potential to reduce PVC-BSIs rates of through multimodal intervention [32, 56].

This protocol study will include the facilitation element based on the PARIHS framework, a key aspect with the potential to make substantial contributions to knowledge in this area [26, 41].

## Abbreviations

CPGs: Clinical practice guidelines
CRBSI: Catheter-related bloodstream infections
C-RCT: Cluster-randomized controlled trial
EBCP: Evidence-based clinical practice
EBPQ: Evidence-Based Practice Questionnaire
EKM: Effective knowledge mobilization
FIRE: Nurses facilitating implementation of research evidence
hFIRE: Hospital leaders
HLOS: Hospital length of stay
nFIRE: Hospital ward nurses
NWI: Nursing Work Index
PARIHS: Promoting Action on Research Implementation in Health Services
PVC-BSI: Bloodstream infections associated with PVCs
PVCs: Peripheral venous catheters
